##### Test group

For standard care, damage-controlled resuscitation strategy is used, only BRS during fluid resuscitation is used, 500 ml/time is used, dosing rate of ≤ 10 ml/kg/h is used, SBP at 80–90 mmHg is maintained, and the total amount is less than 3L during the resuscitation for the first 6 h. Investigators will evaluate whether the patient’s shock state is corrected before each administration. If the resuscitation is successful, the drug will be stopped, and if the shock persists, the drug will be continued.

##### Control group

For standard care, damage-controlled resuscitation strategy is used, only LRS during fluid resuscitation is used, 500 ml/time is used, dosing rate of ≤ 10 ml/kg/h is used, SBP at 80–90 mmHg is maintained, and the total amount is less than 3L during the resuscitation for the first 6 h. Investigators will evaluate whether the patient’s shock state is corrected before each administration. If the resuscitation is successful, the drug will be stopped, and if the shock persists, the drug will be continued.

#### Cessation of study care

For this study, successful shock resuscitation (end of study care) will be defined as the last intravenous injection of BRS /LRS investigator who evaluated the patient’s shock state and believed that shock resuscitation had achieved success.

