### Eligibility criteria

#### Inclusion criteria

Patients with THS [39, 40] (Table 1 shows the diagnostic criteria for THS)Age ≥ 18 years

**Table 1 Tab1:** The diagnostic criteria for THS. Patients who at the same time meet Clinical history, Vital signs^1^, and any three of Vital signs^2^ will be diagnosed as THS

Clinical history	Vital signs^1^	Vital signs^2^
There are traumas that cause hemorrhage (such as road traffic injuries)	(1) Systolic blood pressure (SBP) < 80 mmHg, or mean arterial pressure < 65 mmHg, or a decrease of ≥ 40 mmHg from baseline. (2) Lactate level > 2 mmol/L.	(1) Consciousness changes, includes unresponsiveness, disorientation, and confusion. (2) The skin is wet and cold with vasoconstriction and cyanosis floridis, capillary filling time > 2 s. (3) Urine output < 0.5 ml/kg/h. (4) Pulse rate > 100 beats/min or untouchable, shock index > 1.0.

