#### Initiation of study care

When patients are enrolled in the trial, they will receive standard care and be resuscitated with fluids depending on the study arm. The first 6 h of resuscitation will be administered with BRS or LRS for early resuscitation only. After early resuscitation, the blood products will be given for resuscitation depending on the patient’s condition. Moreover, the patient’s blood sample will be collected before the fluid resuscitation. After the patient enters the study arm, only the fluid type corresponding to the study arm is used for resuscitation. Given that fluid is 500 ml/time, the administration speed is ≤ 10 ml/kg/h, and the total amount is less than 3L during the resuscitation for the first 6 h. Albumin can be used for resuscitation when necessary.

Enrolled patients will be block randomized to either study arm (Fig. 3 shows the drug application process).

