**Fig. 3 Fig3:**
[figure not shown]
Drug application process

Clinical criteria of successful shock resuscitation include:(A)SBP was maintaining at 80–90 mmHg(B)Heart rate was less than or equal to 100 bpm/min(C)A pulse of the aorta was palpable(D)Increased cardiac output (greater than or equal to 4.0L/min)(E)Improved peripheral perfusion (ruddy and dry skin, capillary refilling time less than 2 s)(F)Mixed venous oxygen saturation is greater than or equal to 60% and arterial oxygen saturation greater than or equal to 80%(G)The urine volume was greater than that of 0.5 ml/(kg min)(H)Consciousness improvement(I)Lactate level ≤ 2 mmol/L

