### Detailed outcome measures collected

#### Duration of shock

The time point at which the patient began in the shock state and the time point at which shock resuscitation was successful during the entire trial process will be recorded, and the shock duration will be calculated.

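### The urine criterion for successful resuscitation is printed 60 times too high, and the cessation section, as printed, makes the last injection the end point of co-primary shock duration

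*Protocol article*

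**What the plan says.** All references are to the Protocol article.

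- **Duration of shock** (under Detailed outcome measures collected) ends the endpoint at successful resuscitation: "the time point at which shock resuscitation was successful during the entire trial process will be recorded". It names no criteria and refers to no other section.
- **The list below Fig. 3** opens with "Clinical criteria of successful shock resuscitation include" and gives nine items, A to I. It does not say whether all nine must hold. Item G reads "The urine volume was greater than that of 0.5 ml/(kg min" (closing bracket left off here).
- **Table 1**, which defines shock at entry, uses "Urine output < 0.5 ml/kg/h".
- **Cessation of study care** says that, for this study, success is "defined as the last intravenous injection of BRS /LRS investigator who evaluated the patient’s shock state and believed that shock resuscitation had achieved success". The sentence is garbled. It adds in brackets that the end of study care is meant.
- **Test group** and **Control group** have the investigator assess the shock state before each administration: "If the resuscitation is successful, the drug will be stopped, and if the shock persists, the drug will be continued".
- **Initiation of study care** limits the rate to 10 ml/kg/h, and "the total amount is less than 3L during the resuscitation for the first 6 h". It then adds: "After early resuscitation, the blood products will be given for resuscitation depending on the patient’s condition".
- **Sample size** requires both co-primary endpoints to be met. **Blinding** describes an open trial.

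**The concern.** Two printed statements bear on when shock ends, and each has a defect.

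The first is a threshold. Criterion G belongs to the only list of clinical signs that the article gives for success. A unit of minutes in place of hours turns an ordinary sign of renal perfusion into a urine flow that patients in shock do not reach. If G is required, nobody meets the list as printed. If staff quietly use the hourly unit, the trial is run on a criterion that the protocol does not contain.

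The second is a definition. The cessation section defines the same term that ends shock duration, and by its wording the definition is an injection. The arm descriptions instead put success at a clinical check that follows an injection and stops further dosing.

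At stake is a clear, reproducible end time for an endpoint that must succeed for the trial to succeed, in a setting where the assessor knows the arm.

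**Working it through.** **Step 1. The plan's own figure for this endpoint.** Inputs from Sample size: 3 h against 1.5 h, SD 4 h, one-sided alpha 0.025, power 0.80, 10% loss.

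- Normal approximation: n = 2 × 4² × (1.960 + 0.842)² / 1.5² = 111.7, so 112 per arm.
- The exact t-test gives 113 per arm (power 0.801).
- With loss: 113 / 0.9 = 125.6, so 126 per arm and 252 in total.

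The stated 113 and 252 are reproduced. Nothing below changes them.

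**Step 2. The unit in criterion G.**

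- As printed: 0.5 ml/kg/min × 60 min/h = 30 ml/kg/h.
- Against Table 1: 30 / 0.5 = 60.
- Against the maximum study-fluid rate: 30 / 10 = 3.

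These ratios hold at any body weight. For scale, with assumed weights of 50, 70 and 90 kg:

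| Weight (assumed) | Criterion G as printed | Table 1 threshold | Criterion G over 6 h |
|---|---|---|---|
| 50 kg | 1.5 L/h | 25 ml/h | 9.0 L |
| 70 kg | 2.1 L/h | 35 ml/h | 12.6 L |
| 90 kg | 2.7 L/h | 45 ml/h | 16.2 L |

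The study fluid allowed over those 6 h is below 3 L. A patient would have to pass urine at three times the fastest rate at which study fluid may be given.

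**Step 3. What success means in each section.**

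| Section | What it makes success | When it falls |
|---|---|---|
| List below Fig. 3 | Clinical signs A to I; all or some not stated | When the signs are found |
| Test group, Control group | Investigator's check before the next dose | After the last injection, since success stops the drug |
| Cessation of study care | Last injection, with the investigator's belief in success | At the last injection, if taken word for word |
| Duration of shock | Not defined | Any time during the trial |

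The first two rows fit together: signs are checked, and a positive check stops the fluid. The third row, taken word for word, does not fit them, because the check that establishes success comes later than the injection. The fourth row does not say which of the others applies.

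**Step 4. Can an effect on the treatment difference be computed?** No. That would need the share of patients whose recorded end differs between the readings, the length of the gap, and how both differ by arm. The article gives none of these. A gap equal in both arms would leave the difference unchanged, and if the center already times success by clinical assessment the gap is zero.

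**The case against.** The sections can be read as one process. The cessation sentence stands under a heading about ending study care, carries a bracketed gloss to that effect, and goes on to an investigator who evaluated the patient. It is therefore more likely a rule for stopping the drug than a time stamp for the endpoint. Duration of shock covers the whole trial, which suits a clinical time point better than an injection time. The unit is a slip whose intended value is visible in Table 1. The list says only what the criteria include, so G may not be mandatory. And how a time is stamped (start of infusion, end of infusion, or assessment) is detail that an article may leave to the full protocol or case report form.

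Most of this stands. The stopping-rule reading is the likelier one, and the time-stamp detail is not held against the article. Two things remain. The printed sentence still defines the very term that ends a co-primary endpoint, and in a way that does not match the arm descriptions. And criterion G is a threshold in the list that defines success, not background text, so a wrong unit there is an error in the plan even if staff would read past it.

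A reader might go further and infer that patients who recover after the last dose, for instance at the volume limit or later on blood products, will be timed too early, and that this biases the comparison. The documents do not support that: no section orders the end of shock to be moved back to the last injection. Nor do they establish two rival endpoint definitions. A reader might also suspect an effect that differs by arm, because the list includes a lactate limit and only the control fluid contains lactate. That is conceivable, but nothing in the article fixes its size or shows that it occurs.

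**Conclusion.** The point holds in a limited form.

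- **Criterion G is wrong as printed.** It stands at 30 ml/kg/h against 0.5 ml/kg/h in Table 1, a factor of 60 that needs no assumption. That the list cannot realistically be met follows only if G is required, which the article leaves open.
- **The cessation sentence, as printed, defines success as the last injection.** It is probably meant to define only the end of study fluid. The list and the arm descriptions place success at a clinical assessment after that injection, and Duration of shock does not say which applies.
- **No size or direction of bias follows from the document**, and the sample size stands.

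These are drafting corrections to a co-primary endpoint. They are worth making before analysis, because the end is judged with the arm known and both co-primary endpoints must be met.

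**What to change.** 1. In criterion G, replace 0.5 ml/(kg min) with 0.5 ml/kg/h, as in Table 1.
2. Reword Cessation of study care so that it defines only the end of study fluid.
3. In Duration of shock, set the end at the first documented assessment at which the criteria below Fig. 3 are met, whatever treatment is then running. State whether all nine criteria or a named subset are required. Without that, the end time stays open even after the unit is corrected.
4. Apply the same rule to patients already enrolled (recruitment began on 1 May 2021), using source records, before the data are analysed.

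The cost is one corrected unit, two reworded sentences and a small amount of source-record checking. Some recorded durations may change. The sample size does not.

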#### Provisions for post-trial care

This study has insured the subjects who participated in the trial.

### Outcomes

#### Primary endpoint

(A)Duration of shock(B)Lactic acid clearance rate of 6 h

### Secondary endpoints

(A)The amount of drug use, the total amount of resuscitation fluid, and the use of vasoactive drugs was compared in each study arm.(B)The total number of deaths and mortality was compared. The Kaplan–Meier survival curve was drawn, and the 7-day mortality of patients in each study arm was compared.(C)The levels of inflammatory mediators (PLA2, TNF- α, IL-6, PCT, CRP) were compared in each study arm.(D)The recurrence rate of shock and the complications of survival cases (ARDS, AKI, TIC, MODS, etc.) were compared among the study arms.(E)Blood coagulation and platelet function (PT, APTT, TT, INR, ACT, Fib, VEM) were compared among different study arms and before and after treatment.(F)Body temperature and acidosis (T, PH, BE, Lac, PaCO_2_, HCO_3_^−^) was compared among different study arms and before and after treatment.(G)The mechanical ventilation time, EICU hospitalization time, and total hospitalization time of patients in each study arm was compared.

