## Abstract

**Background:**

Traumatic hemorrhagic shock (THS) is the main cause of death in trauma patients with high mortality. Rapid control of the source of bleeding and early resuscitation are crucial to clinical treatment. Guidelines recommend isotonic crystal resuscitation when blood products are not immediately available. However, the selection of isotonic crystals has been controversial. Sodium bicarbonate Ringer solutions (BRS), containing sodium bicarbonate, electrolyte levels, and osmotic pressures closer to plasma, are ideal. Therefore, in this study, we will focus on the effects of BRS on the first 6 h of resuscitation, complications, and 7-day survival in patients with THS.

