### Objectives

By comparing the differences in duration of shock and the lactic acid clearance rate at each time point when early fluid resuscitation was performed in the test group and control group. To identify whether early fluid resuscitation using BRS can reduce the complication rate and improve 7-day survival in patients with THS.

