#### Complications

Complications (ARDS, AKI, TIC, MODS, etc.) that occurred during the entire study process will be recorded and confirmed through corresponding diagnostic methods.

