#### Duration of mechanical ventilation, renal replacement therapy

The days of mechanical ventilation, hemodialysis, or hemofiltration are calculated and recorded.

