#### EICU days and length of stay

Hospital stays and length of EICU days will be recorded. If the patient is hospitalized at any time of the day, that day will be regarded as the hospitalization day. If the patient is in the EICU at any point on the calendar day, that day will be considered EICU day.

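### Complications are compared only among survivors, a group formed after randomisation, so the comparison does not answer the stated objective and can point the wrong way

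*Protocol article*

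**What the plan says.** All references are to the Protocol article.

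- **Secondary endpoints, item D:** "The recurrence rate of shock and the complications of survival cases (ARDS, AKI, TIC, MODS, etc.) were compared among the study arms". The restriction to survivors is explicit for complications. Whether it also covers recurrence of shock is unclear from the grammar.
- **Objectives:** "To identify whether early fluid resuscitation using BRS can reduce the complication rate and improve 7-day survival in patients with THS". The complication question is asked of patients with the condition, and an effect on survival is part of the same hypothesis.
- **Detailed outcome measures, Complications:** "Complications (ARDS, AKI, TIC, MODS, etc.) that occurred during the entire study process will be recorded". Collection is not limited to survivors.
- **Abstract, Background:** "Traumatic hemorrhagic shock (THS) is the main cause of death in trauma patients with high mortality". No mortality rate is given anywhere.
- **Exclusion criteria:** the last item covers patients who abandon treatment or die in the course of the trial. The Stopping criteria also name death within 1 h of the intervention.
- **Secondary endpoints, item G:** "The mechanical ventilation time, EICU hospitalization time, and total hospitalization time of patients in each study arm was compared". The detailed sections add only that "The days of mechanical ventilation, hemodialysis, or hemofiltration are calculated and recorded" and "Hospital stays and length of EICU days will be recorded", with a rule for counting calendar days. They do not say how a death enters these durations.

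**The concern.** Randomisation makes the two arms comparable as allocated. It does not make the survivors of one arm comparable with the survivors of the other if the fluid affects who survives. Here a survival effect is hoped for, in a condition described as highly lethal. A patient who develops multiple organ dysfunction and dies of it contributes nothing to item D, although the event is on the case report form.

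Reducing complications is a named objective of the trial. If one fluid keeps alive some patients who would have died on the other, and those patients are sicker than the rest, its survivors will show more complications even when it causes none. The survivor-only result could then be read as a safety signal against the better fluid, or as reassurance about the worse one.

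This is not a detail left to an analysis plan. The text itself fixes the analysis population, and it does not match the population in the objective.

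**Working it through.** The plan states no expected mortality or complication rate and no sample size for this endpoint, so there is no figure of its own to reproduce. Every rate below is an assumption.

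**Set-up.** Divide patients by what would happen on each fluid. With mortality of 20% on control and 10% on test, and nobody dying on test who would have survived on control:

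- 0.80 survive on either fluid; 30% of them have a complication on either fluid (no true effect);
- 0.10 survive only on the test fluid (the extra survivors); a share s of them have a complication;
- 0.10 die on either fluid.

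**Survivor-only rate (item D as written).**

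- Control: 0.24 / 0.80 = 30.0%.
- Test: (0.80 × 0.30 + 0.10 × s) / 0.90.
  - s = 0.6: 0.30 / 0.90 = 33.3%, an excess of 3.3 points.
  - s = 0.8: 0.32 / 0.90 = 35.6%, an excess of 5.6 points.

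**Death or complication, all randomised.**

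- Control: 0.20 + 0.24 = 44%.
- Test: 0.10 + 0.24 + 0.10 × s = 40% (s = 0.6) or 42% (s = 0.8).

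The two summaries point in opposite directions.

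**Other mortality pairs, same 30% and s = 0.6 to 0.8.**

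| Mortality, control vs test | Test survivor-only rate | Excess over 30% |
|---|---|---|
| 10% vs 5% | (0.27 + 0.05s) / 0.95 = 31.6% to 32.6% | 1.6 to 2.6 points |
| 20% vs 10% | 33.3% to 35.6% | 3.3 to 5.6 points |
| 30% vs 20% | (0.21 + 0.10s) / 0.80 = 33.75% to 36.25% | 3.75 to 6.25 points |

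**Where the sign changes (20% vs 10%).**

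- s = 0.3: 0.27 / 0.90 = 30.0%. No bias.
- s = 0.2: 0.26 / 0.90 = 28.9%. The bias reverses, to −1.1 points.
- If the test fluid truly lowers the rate from 30% to 20% in those who survive on either fluid, with s = 0.6: (0.16 + 0.06) / 0.90 = 24.4% against 30%. The comparison then still points the right way.

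**Does counting complications in everyone suffice?** Let d be the share of deaths preceded by a complication.

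- Control: 0.24 + 0.20d. Test: 0.24 + 0.10s + 0.10d. Difference: 0.10(s − d).
- With d = 0.3 and s = 0.6: 30% vs 33%.

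This compares the groups as randomised, but it can still favour the arm with more deaths, because death cuts short the time in which a complication can occur. It has to be read beside the composite.

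**Durations (item G), if deaths enter as plain day counts.** Assume 14 hospital days for survivors, 2 for deaths and 14 to 20 for the extra survivors, at 20% vs 10% mortality.

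- Control: 0.80 × 14 + 0.20 × 2 = 11.6 days.
- Test: 0.80 × 14 + 0.10 × (14 to 20) + 0.10 × 2 = 12.8 to 13.4 days, so 1.2 to 1.8 days longer on the life-saving fluid.
- The direction is not assured. With ventilation of 1 day for survivors, 3 for deaths and 2 for the extra survivors, control is 0.80 + 0.60 = 1.4 days and test is 0.80 + 0.20 + 0.30 = 1.3 days.

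**The case against.** **Direction.** A reader might infer that a life-saving fluid must look worse and a harmful one better. The documents do not support that. They give no mortality or complication rates, and the sign depends on how sick the extra survivors are: with equal rates there is no bias, and with a lower rate it reverses. Any true reduction in complications, which the Objectives hypothesise, works against the bias and may outweigh it. This part of the objection stands in full. It limits the claim to what can happen, and it does not rescue a comparison whose sign depends on a mix of survivors that nobody can observe.

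**Remedy.** Counting complications in all randomised patients can give nearly the same picture (30% vs 33% above), and the composite favours the test fluid here because it contains mortality, which item B already compares. Both statements are true. They are the reason to report the two measures together.

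**Durations.** A reader might also infer that the plan fixes ventilation, EICU and hospital time as raw counts in which an early death passes for a good result. It does not say so. It is silent on deaths, and an analysis plan that is not shown may supply the rule. Stay in days is also a legitimate description of resource use when set beside mortality. This remains a secondary point only.

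**Cost.** The Complications section mentions recording and confirmation but no dates, whereas the sections on shock recurrence and surgical episodes do name time points. If the exclusion item on deaths is applied after randomisation, the data needed for the correction may be missing. Both cautions stand and are taken up in the fix.

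**Conclusion.** The concern holds for complications. Item D selects its population by a post-randomisation outcome, does not match the population in the Objectives, and discards fatal complications that the trial records. The resulting comparison can be biased and can point the wrong way.

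Under the assumed rates, a fluid with no effect on complications in patients who survive either way shows a spurious excess of about 1.6 to 6.25 percentage points across mortality of 10% vs 5% up to 30% vs 20%. At 20% vs 10% the survivor-only rates are 30% vs 33-36%, against 44% vs 40-42% for death or complication. These figures illustrate a mechanism and do not predict this trial's result. They rest on the extra survivors having complications at 60-80% against 30% in the others.

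For the durations in item G the documents support only a request for clarity. The primary endpoints and the sample size of 400 are unaffected. The change should be made because the affected comparison serves a named objective and the correction is small.

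**What to change.** 1. In item D, delete the words that limit complications to survivors, and say whether recurrence of shock is also compared in all randomised patients.
2. Compare complications in all randomised patients, counting every one that occurs before death and treating death as a competing event.
3. Report death or complication by day 7 beside it, since the complication count alone can still favour the arm with more deaths. Show its two components separately, because the composite is partly driven by mortality.
4. State that the exclusion item on patients who die in the course of the trial removes no randomised patient from this analysis, and reconcile it with the Stopping criteria on early death.
5. As a secondary point, either present the durations in item G together with mortality or analyse them with death ranked as the worst outcome. Ventilator-free or EICU-free days to day 7 are less suitable, because a patient ventilated or in the EICU for all seven days would score 0, the same as a death.

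**Cost.** Mostly wording and one derived variable, with no extra visits. Two conditions apply: the case report form must give the timing of complications, which the Complications section does not mention, and data on randomised patients who died must have been kept.
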